## Abstract

**Background:**

Overweight, obesity, and associated comorbidities are a pressing global issue among children of all ages, particularly among low-income populations. Rapid weight gain (RWG) in the first 6 months of infancy contributes to childhood obesity. Suboptimal sleep-wake patterns and gut microbiota (GM) have also been associated with childhood obesity, but little is known about their influences on early infant RWG. Sleep may alter the GM and infant metabolism, and ultimately impact obesity; however, data on the interaction between sleep-wake patterns and GM development on infant growth are scarce. In this study, we aim to investigate associations of infant sleep-wake patterns and GM development with RWG at 6 months and weight gain at 12 months. We also aim to evaluate whether temporal interactions exist between infant sleep-wake patterns and GM, and if these relations influence RWG.

**Methods:**

The Snuggle Bug/ Acurrucadito study is an observational, longitudinal study investigating whether 24-h, actigraphy-assessed, sleep-wake patterns and GM development are associated with RWG among infants in their first year. Based on the Ecological Model of Growth, we propose a novel conceptual framework to incorporate sleep-wake patterns and the GM as metabolic contributors for RWG in the context of maternal-infant interactions, and familial and socio-physical environments. In total, 192 mother-infant pairs will be recruited, and sleep-wake patterns and GM development assessed at 3 and 8 weeks, and 3, 6, 9, and 12 months postpartum. Covariates including maternal and child characteristics, family and environmental factors, feeding practices and dietary intake of infants and mothers, and stool-derived metabolome and exfoliome data will be assessed. The study will apply machine learning techniques combined with logistic time-varying effect models to capture infant growth and aid in elucidating the dynamic associations between study variables and RWG.

**Discussion:**

Repeated, valid, and objective assessment at clinically and developmentally meaningful intervals will provide robust measures of longitudinal sleep, GM, and growth. Project findings will provide evidence for future interventions to prevent RWG in infancy and subsequent obesity. The work also may spur the development of evidence-based guidelines to address modifiable factors that influence sleep-wake and GM development and prevent childhood obesity.

## Background

### Early rapid weight gain in infancy contributes to childhood obesity

Early childhood obesity is a serious health problem. In 2019, 38.2 million U.S. children less than 5 years old were overweight or obese, with greater prevalence among low- and middle-income families [1]. Of those under 2 years, 8.1% had high weight-for-recumbent length (i.e., at or above the 95th percentile) [2]. Further, obese children are more likely to become obese adults [3]. Rapid weight gain (RWG) in the first 6 months of infancy, defined as a greater than 0.67 positive change in weight-for-age Z-score (difference between centile lines on standard growth charts) [4], is associated with greater total weight gain from 0 to 12 months and greater weight-for-length and weight-for-age percentiles at 36 months [5]. It also increases the odds of obesity across the life course [6–9] and relates to adverse health outcomes later in life, including hypertension, diabetes, and cardiovascular diseases [10]. Further, RWG in the first 3 months is more predictive of poor cardiometabolic outcomes than any other 3-month period in the first year of life [11]. Despite robust, globally diverse cohort data accounting for numerous confounding factors present from conception to birth on childhood obesity, few studies have focused on RWG determinants and timing in the birth-to-6-month period.

### Suboptimal sleep-wake patterns are important risk factors for childhood obesity but understudied in infants in relation to RWG

Systematic reviews and meta-analyses conclude that short sleep duration is associated with childhood overweight/obesity [12, 13]. Prospective cohort studies suggest that short sleep duration (parent reported < 12 h) in early infancy is associated with greater body mass index (BMI) at 24 months [13], a two-fold odds of childhood obesity [14], and greater weight-for-length and excess weight gain by 24 months [15]. However, evidence suggesting that longer sleep duration in infancy is associated with healthier body composition remains uncertain [16]. Sleep is a multidimensional construct composed of other components beyond sleep duration that contribute to obesity risk, including sleep-wake timing and patterns (e.g., circadian rhythmicity). Greater nap frequency in infancy [17] and more rapid sleep stage development (i.e., active and quiet) among preterm infants [18] also predict subsequent growth in length and favorable weight outcomes, respectively. Further, data from three randomized controlled trials suggest that infant sleep promotion (i.e., adequate sleep duration, not feeding to soothe baby to sleep) influences adiposity. Infants receiving interventions with a sleep component had lower BMI z-scores [19, 20] and weight-for-length percentiles [21], were less likely to be overweight/obese [19], and had slower weight gain rates [19] than non-sleep interventions (follow-up from 6 months to 5 years). However, no studies have explored associations between sleep-wake patterns and RWG, with the exception of our single, previous study [5]. Our results indicated that newborns (1 month) with later bedtimes (≥10:00 PM) were more likely to experience RWG in their first 6 months than newborns who went to bed earlier [5]. Further, newborns taking more daytime naps were significantly less likely to experience RWG [5]. Also, previous studies have rarely used actigraphic monitoring (i.e., movement-based recording with a wearable sensor) of infants to provide a comprehensive, prospective assessment of sleep patterns [22], particularly in association with early infant growth. One exception was a prospective study that found shorter nocturnal sleep duration measured via actigraphy at 8 months of age was associated with higher odds for greater weight-for-length at 24 months [15].

### Gut microbiota (GM) is associated with childhood obesity, but little is known about microbial influences on infant RWG

The majority of GM development including colonization and maturation occurs within the first 3 years of life [23]. Previous studies have linked breast vs. formula feeding [24–30], birth delivery mode [26, 30, 31], maternal pre-pregnancy weight [30, 32], and perinatal antibiotic exposure [33, 34] to unique differences in the ecology of the infant’s commensal GM. Two case-control studies matching participants for mode of birth delivery, birth weight, breastfeeding duration, antibiotic exposure, and gestational age suggest that decreased *Bifidobacteria* relative abundance, particularly at 3 months [35], is associated with childhood obesity [35, 36]. Increases in *S. aureus* relative abundance at 6 and 12 months have been associated with overweight at 7 years [35], while greater relative abundance of *B. fragilis* at 6 months was linked to overweight at 10 years [36]. Elevated counts of *B. fragilis* as early as 1 month have been associated with higher BMI z-scores across ages 1–10 years [37]. Differential trajectories of microbial communities are established during development [35] and up to 10% of GM fluctuate throughout the day [38]. Their influence on infant growth may vary depending on environmental exposures. Recent data have indicated that male and female infants differ in their response to GM changes with regard to early-life weight gain [39] and that maternal-child interactions play an important role in establishing GM communities and influencing infant growth [34, 40]. Delays in colonization of beneficial microbes in infancy are also associated with adiposity [41]. However, gut microbial influences on infant RWG are understudied. In addition, to date no large scale longitudinal studies have defined how early postnatal development of the gut microbiota is influenced by environmental factors and how, in turn, the microbiota influences host gene expression.

### Evaluation of the influence of the interaction between sleep-wake patterns and GM development on infant growth is scarce

Though sleep loss, fragmentation, and circadian misalignment are proposed stressors with the potential to influence GM and induce gut dysbiosis [42], limited pediatric studies on sleep-wake pattern and GM relationships exist. One study of older infants found that actigraphy-assessed nocturnal sleep duration at 6 months was associated with changes in GM beta-diversity [43]. Sleep metrics at 12 months were associated with GM beta-diversity. Specifically, greater fragmentation was associated with greater *Bacteroides* and lower *Lachnospiraceae* prevalence, and greater bedtime variability was associated with greater *B. longum* yet lower prevalence of other *Bifidobacterium* species [43]. Among adults, a within-subject crossover study (*n* = 9) found that 2 nights of partial sleep deprivation (4.25 vs. 8.5 h) increased the Firmicutes:Bacteroidetes ratio, led to greater relative abundance of *Coriobacteriaceae* and *Erysipelotrichaceae* families and lower relative abundance of *Tenericutes* [44]. Conversely, a study of 11 participants who underwent two rounds of partial sleep restriction (i.e., 4 nights with 4 h followed by 5 nights of 12 h) found no significant changes in GM composition [45]. A cross-sectional study of 37 community-based older adults found that better sleep quality was associated with greater *Verrucomicrobia* and *Lentisphaerae* relative abundance [46]. To our knowledge, there are, to date, no studies of the GM as a mediator for circadian sleep-wake disruption and subsequent infant RWG.

## Methods/design

### Theoretical framework

The Ecological Model of Growth (EMG) combines human ecology and epidemiology to evaluate factors that influence child health outcomes in the context of broader environmental constructs (parent, family, and home) [47, 48]. It has been validated as an effective tool for studying maternal and child factors that contribute to infant growth [49–51], but has not been used to study how EMG constructs influence RWG via the GM and sleep. Based on the EMG, we propose a conceptual framework that incorporates sleep-wake patterns and the GM as metabolic contributors for RWG in the context of socio-physical environments, to early-onset childhood obesity (Fig. 1). In the framework, major interactions to be explored or controlled for are (1) GM variation in response to child feeding mode and sleep-wake patterns, (2) maternal-child interactions (e.g., influence over sleep and soothing habits), (3) feeding interactions (e.g., parenting style, scheduled/on-demand feeding), and (4) environmental exposures.

**Fig. 1 Fig1:**
[figure not shown]
Ecological model of rapid weight gain

### Aim and design

This study is designed as a five-year observational longitudinal study to investigate how 24-h sleep-wake patterns and GM influence RWG among infants in their first year. In this study, we aim to:
Investigate associations of infant sleep-wake patterns with subsequent RWG at 6 months and weight gain at 12 months using Time-Varying Effect Models (TVEM). We hypothesized that infants with suboptimal sleep-wake patterns (e.g., short sleep duration, poorer sleep quality [e.g., sleep percent, number of long awakenings], later bedtimes, and greater sleep-wake timing variability) will be more likely to experience RWG at 6 months and have greater total weight gain at 12 months than infants with optimal sleep-wake patterns.Investigate associations of GM development with RWG at 6 months and weight gain at 12 months. We hypothesized that infants with lower GM diversity, decreased relative abundance of beneficial microbes (e.g., *Bifidobacteria*), and increased pathogen abundance (e.g., *Staphylococcus*) across time will be more likely to experience RWG at 6 months and have greater total weight gain at 12 months.Evaluate whether temporal interactions exist between infant sleep-wake patterns and GM development, and if these relations influence RWG. We hypothesize that (1) infants with short sleep duration, poorer sleep quality, later bedtimes, and greater sleep-wake timing variability will exhibit lower GM diversity, decreased relative abundance of beneficial microbes, and increased pathogen abundance than infants with optimal sleep-wake patterns; and (2) infant sleep-wake patterns and GM development will have a synergistic effect on RWG, with suboptimal development of both factors increasing risk for RWG compared to either factor independently.

### Power analysis and target population

Using the Hedeker et al. approach [52], for a test of a between groups linear trend difference (comparing normal infant growth to those with RWG), equal sample sizes, 6 time points, a correlation among the repeated measures of 0.5, a compound symmetry structure, a medium effect size of one third of a standard deviation, an α of 0.05, and a power of 0.8, a total sample size of 184 participants (includes for estimated 20% attrition) is needed for Aim 1. To power for Aims 2–3, we reduced all EMG constructs (Fig. 1) into a single virtual covariate to facilitate computation. We then generated simulated data based on a mixed effect logistic regression model that included the virtual covariate, a sleep pattern variable and a GM diversity variable, each randomly drawn from a normal distribution and having six repeated measures. We fixed the effect size of the virtual covariate to be medium (Cohen’s f2 = 0.15), and varied the effect sizes of the sleep pattern variable and the GM diversity variable between medium (f2 = 0.15) and large (f2 = 0.35) as were observed in unpublished preliminary data. Figure 2 shows that 160 infants are required to achieve a power of 0.8 to detect a significant medium-sized effect at α = 0.05. Adjustment for a 20% attrition rate requires that we recruit 192 mother-infant pairs.

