#### Infant sample subject eligibility

Inclusion criteria include full-term (≥37 weeks of gestation) singleton infants who have no growth abnormality or other endocrine, chromosomal, or genetic abnormality, or severe illness-related comorbidity that could impact growth and development. Exclusion criteria are (1) mother-infant pairs who are not discharged together from the hospital; or (2) infants born with congenital abnormalities or conditions that may be expected to result in developmental delays or birth weights < 2500 g or > 4000 g.

Potential participants will be identified by providers and research staff through in-house recruitment from obstetrics and pediatric units at a local public hospital system, and a network of Supplemental Nutrition Program for Women, Infants, and Children (WIC) clinics. Advertisements will also be distributed through social media, Arizona State University (ASU) Institutional listservs, word-of-mouth, sharing flyers with active study participants, community events, and health professional referrals from clinical and community partners. Eligible participants will provide their contact information. Regular telephone calls, emails, or text messaging contacts will be made to determine birthdate, if eligibility is maintained, and to schedule the first in-home visit. Secondary (e.g., family member, friend) contacts will be obtained in case participants lose phones or change numbers. Enrollment and consent will occur at the first in-home visit at 3-weeks post-delivery.

Study procedures are designed to capture periods during which important neurodevelopmental milestones tend to occur, which have also been associated with early life adiposity [53] (Fig. 3). In-home visits will be conducted in near time to 3 and 8 weeks, and 3, 6, 9, and 12 months postpartum. Along with major neurodevelopmental milestones that tend to occur at these ages, important shifts in infant feeding [54–56], sleep-wake pattern development [57–61], and GM community changes that have previously been associated with infant and childhood weight status [34, 37, 62–64] tend to coincide with these time periods.

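### The Aim 1 power statement assumes equal RWG and normal-growth groups, which an unstratified cohort cannot be assumed to yield, and under a two-sided test its 184 matches a constant difference rather than the stated linear trend

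*Protocol article*

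**What the plan says.** The section Power analysis and target population describes the Aim 1 calculation as being "for a test of a between groups linear trend difference (comparing normal infant growth to those with RWG), equal sample sizes, 6 time points". The other inputs are "a correlation among the repeated measures of 0.5, a compound symmetry structure", "a medium effect size of one third of a standard deviation", and "an α of 0.05, and a power of 0.8". The result is that "a total sample size of 184 participants (includes for estimated 20% attrition) is needed for Aim 1". A separate simulation for Aims 2 and 3 gives 160 infants, raised to 192 for attrition, and 192 is the recruitment target.

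The paragraph does not say whether the test is one- or two-sided, where along the trend the third of an SD applies, or how the 20% loss is spread over the visits.

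Elsewhere, the Background gives RWG as "defined as a greater than 0.67 positive change in weight-for-age Z-score" over the first 6 months. The section Assessment of RWG and infant growth makes it the primary outcome. Aim and design describes an observational longitudinal study. The two eligibility sections contain no matching, enrichment or stratification on RWG, and enrolment is at 3 weeks, before RWG status can be known. The visits are unequally spaced: "In-home visits will be conducted in near time to 3 and 8 weeks, and 3, 6, 9, and 12 months postpartum".

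**The concern.** There are two separate problems in one sentence.

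1. **Group split.** The calculation treats RWG and normal growth as two arms of equal size. Nothing in the design allocates or balances them; the split is whatever the cohort produces. For a fixed total, an unequal split lowers power for any two-group contrast, so the 80% is optimistic whichever contrast was used.

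2. **Contrast.** The sentence names a trend test, but the number that comes out is, under a two-sided test, the number for a constant difference. A trend that starts at zero and reaches the same third of an SD at the last visit needs more infants.

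At stake is whether the 80% power claimed for the first aim belongs to the test described and to the groups the study will have.

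**Working it through.** **Inputs from the article:** 6 visits, correlation ρ = 0.5 with compound symmetry, d = 1/3 SD, α = 0.05, power 0.80, 20% attrition, equal groups, 192 recruits.

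**Assumptions, not in the article:** two-sided test unless stated otherwise; retention falling evenly over the visits (1.00, 0.96, 0.92, 0.88, 0.84, 0.80); RWG share p of 20% to 40%.

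**Formula.** For a contrast c over the visits and a vector δ of group differences,

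n per group = 2(z_α + z_β)² · c′Vc / (c′δ)².

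V has 1 on the diagonal and 0.5 elsewhere, and each entry is divided by √(r_i r_j) to allow for retention r. Two-sided, (1.960 + 0.842)² = 7.849.

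**Step 1: reproduce 184.** Constant difference, c = (1,…,1), c′δ = 6 × 1/3 = 2.
- No loss: c′Vc = 21, so n = 2 × 7.849 × 21/4 = 82.4.
- With retention: c′Vc = 23.44, so n = 2 × 7.849 × 23.44/4 = 91.99, that is 92 per group and **184** in total.

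**Step 2: the linear trend, 0 to 1/3 SD, equally spaced visits.** c = (−2.5, −1.5, −0.5, 0.5, 1.5, 2.5), c′δ = 17.5/15 = 1.1667.
- No loss: c′Vc = 8.75, so n = 2 × 7.849 × 8.75/1.361 = 100.9, about 202 in total and already above 184.
- With retention: c′Vc = 9.905, so n = 114.2, that is 115 per group and **230** in total.
- With the planned visit ages (weeks converted to months) and the same retention: 107.2 per group, about **214** in total.
- If one third of an SD were instead the average difference along the trend, the requirement with retention would be 28.6 per group, about 58 in total.

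**Step 3: one-sided trend.** (1.645 + 0.842)² = 6.183 replaces 7.849. Equal spacing with graded retention gives 90.0 per group, about 180. Planned visit ages give 73.0 before loss; divided by 0.8 that is 91.3 per group, about 183 to 184.

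**Step 4: unequal groups.** The required total is multiplied by 1/(4p(1−p)), so

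power = Φ( √(N·4p(1−p)/N₅₀) × 2.802 − 1.960 ),

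where N₅₀ is the equal-group total (2 × 91.99 = 184.0 for constant, 2 × 114.24 = 228.5 for trend). Example: N = 192, p = 0.30, constant: 192 × 0.84 = 161.3; √(161.3/184.0) = 0.936; 0.936 × 2.802 − 1.960 = 0.663; Φ = 0.75.

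Two-sided power with 192 recruits:

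| RWG share | Constant 1/3 SD | Trend 0 to 1/3 SD (equal spacing) |
|---|---|---|
| 50% | 0.82 | 0.73 |
| 40% | 0.80 | 0.71 |
| 30% | 0.75 | 0.65 |
| 25% | 0.70 | 0.60 |
| 20% | 0.63 | 0.54 |

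With the planned visit ages (N₅₀ = 214.4), the trend column becomes 0.76 at 50% and 0.74 down to 0.56 at 40% to 20%.

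The constant difference detectable with 80% power at 192 is (1/3)·√(184/(192·4p(1−p))): 0.33 SD at 40%, 0.36 at 30%, 0.38 at 25% and 0.41 at 20%.

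**Step 5: what a 50% share would need.** Half the infants exceed a Z-score change of 0.67 only if the median change is about 0.67. As an illustration only, if weight-for-age Z had SD 1 at both ages and no mean shift, the share above 0.67 would be 1 − Φ(0.67/√(2(1−r))): 32% at between-age correlation r = 0 and 14% at r = 0.8.

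**The case against.** The strongest reply concerns the contrast. A reader might infer from Step 1 that 184 can have come only from a constant-difference calculation and that no trend reading fits. The article does not support that. It states neither sidedness nor dropout pattern, and Step 3 shows that a one-sided trend test lands on about 180 to 184; the hypotheses under Aim and design are directional. The exact match in Step 1 also depends on graded retention. The same constant contrast gives about 206 with a flat 20% loss (82.4/0.8 = 103.0 per group), and about 198 if inflated by 1.2, which is how the same paragraph turns 160 into 192. The two trend readings, 58 and 230, lie on either side of 184, and how the effect is parameterised may rest on the cited method, which is not at hand. All of this stands: the text is ambiguous, and an arithmetic error is not proved. It does not rescue the paragraph, because no one-sided test is stated there or in Statistical analyses, and applying the factor 1.2 to the one-sided trend gives about 175 (planned ages) or 191 (equal spacing), not 184.

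On the group split, a reader might infer that the cohort is certain to be unbalanced and that power will be badly short. That too goes beyond the documents. No RWG share is given, the study recruits through WIC clinics and aims at a high-risk population, and at 40% the constant-difference power at 192 is still 0.80.

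Finally, recruitment is set by the Aims 2 and 3 simulation, which already uses a mixed-effect logistic model with a sleep variable. That is fair, and it is why the shortfall is judged at 192 as well as at 184. But the article presents that simulation for the other aims, and its text gives no RWG share either.

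**Conclusion.** The point holds in a limited form. The equal-groups input does not fit the design whichever contrast was powered, because RWG is an observed outcome in a cohort with no balancing on it. For a constant difference tested two-sided, the stated 80% is kept at 192 recruits only if the RWG share is about 40% or more; at 20% to 30% it is 0.63 to 0.75.

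Separately, under a conventional two-sided test, 184 corresponds to a constant third-of-an-SD difference. A trend from 0 to that value needs about 214 to 230 infants; with equally spaced visits its power at 192 is 0.73 with equal groups and 0.54 to 0.71 at shares of 20% to 40%.

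These sizes rest on three assumptions: two-sided testing, retention falling evenly from 1.0 to 0.8, and an RWG share that the article does not give. The imbalance conclusion is the firmer of the two, since it does not depend on how 184 was obtained.

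**What to change.** Revise the Aim 1 part of the power paragraph to:

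- replace the equal-groups assumption with an expected RWG proportion, its basis and a plausible range;
- state which contrast is powered (constant difference or trend), whether the test is one- or two-sided, what the third of an SD refers to along the visits, and the assumed dropout pattern;
- restate power, or the smallest detectable effect, for the 192 recruits over that range, preferably for the logistic time-varying effect model that Statistical analyses says will be fitted, with RWG as the outcome.

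The cost is one rewritten paragraph and a short recalculation, with no added enrolment. The drawback is that the stated power for Aim 1 will probably look less favourable.

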**Fig. 2 Fig2:**
[figure not shown]
Power simulations for Aims 2 and 3. Each point is an average of 100 simulations

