### Statistical analyses

To evaluate Aim 1, visit-to-visit changes in 24 h sleep and sleep-wake rhythmicity variables and their relationship to occurrence of RWG will be examined with a logistic TVEM. It can reveal critical periods during which changes in sleep-wake patterns accelerate/decelerate infant weight gain [114] and include other covariates with time-invariant effects. The TVEM model can be formulated as,

1$$ logit\;(RWG)={\beta}_0f(t)+{\Sigma}_v\kern0.5em {\beta}_vf(t)V+{\Sigma}_c\kern0.5em {\beta}_cC+\in $$where *f*(*t*) is a smooth function of time *t*, *V* is a set of variables with time-varying effects, *C* is a set of variables with time-invariant effects, *β*_0_, *β*_*v*_ and *β*_*c*_ are the corresponding coefficients, and *ϵ* is normally distributed random errors. We will impose no constraints on the *f*(*t*) function and the *β* coefficients except an assumption of smooth temporal progressions. To fit the model given the collected data, we will use the %TVEM SAS macro [115] and use a P-spline method to select the best-fitting model using knots (splitting points). Significance will be assessed based on the *p*-values of estimated *β* coefficients.

To evaluate Aim 2, we will apply the TVEM in model (1) with representing the alpha and beta diversity scores for each taxon. Because there are hundreds of taxa that may share dependencies, we will compute false discovery rates (FDRs) using the Benjamini–Hochberg procedure [116]. Taxa with FDR < 5% will be regarded as having significant associations. Given the hierarchical structure among taxa, we will further reduce the redundancies among significant taxa by ranking them on Akaike information criterion (AIC) values. Specifically, we will traverse the taxonomic tree (leaves to root) and compute AIC values for each clade. If a parent node has a lower AIC value than any of its child nodes, we will keep the parent node and remove the child nodes from the short-listed taxa.

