To evaluate Aim 3, exploratory analysis will apply principal component analysis to examine if the combination of GM variables and sleep-wake variables can explain a higher variance of RWG than using each class of variables independently. Confirmatory analysis will use model (1) to include the main effects and pairwise interactions between GM diversity scores and sleep-wake variables. Significant p-values and positive coefficients of interaction terms will indicate synergistic effects. However, because there are potentially many GM taxa associated with RWG, model (1) may include too many variables and trivial effects that reduce the statistical power. In this case, we will take a nested approach to test synergies among correlated variables. Specifically, combining the significant variables identified in Aims 1 and 2, we will first test pairwise correlations. We will then group significantly correlated variables using Gaussian finite mixture models [117] that automatically determine the number of clusters. If GM diversity scores and sleep-wake patterns coexist in a cluster, we will use model (1) extended with interaction terms to test synergistic effects. For the proposed exfoliomic data, we will utilize systems biology approaches to illuminate transgenomic cross-talk between host exfoliated intestinal epithelial cells [84] and the genomes of the gut microbiota [83, 118] in a longitudinal cohort.

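### The 0.8 power stated for Aims 2–3 can cover one GM-diversity (or sleep) main effect at α = 0.05, but not the taxon-level FDR rule of Aim 2 or the confirmatory sleep × GM interaction test of Aim 3

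*Protocol article*

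**What the plan says.** Under Power analysis and target population, the protocol article introduces a simulation meant to power Aims 2 and 3. It rests on a "mixed effect logistic regression model that included the virtual covariate, a sleep pattern variable and a GM diversity variable". The virtual covariate has a medium effect, and the effects of the sleep and GM variables are varied "between medium (f2 = 0.15) and large (f2 = 0.35) as were observed in unpublished preliminary data". The result is that "160 infants are required to achieve a power of 0.8 to detect a significant medium-sized effect at α = 0.05". The caption of Fig. 2 assigns the simulation to both aims: "Power simulations for Aims 2 and 3. Each point is an average of 100 simulations".

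Under Statistical analyses, the decision rules are different. For Aim 2 the time-varying effect model is applied taxon by taxon, the article expects hundreds of taxa, p-values go through Benjamini–Hochberg, and "Taxa with FDR < 5% will be regarded as having significant associations". For Aim 3, "Confirmatory analysis will use model (1) to include the main effects and pairwise interactions" of GM diversity scores with sleep-wake variables. Synergy is claimed when an interaction coefficient is significant and positive.

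**The concern.** A power figure belongs to one test: a given effect, threshold and model term. The test described in the power section is a main effect at 0.05. The tests that settle Aim 2 at taxon level and synergy in Aim 3 use a far stricter threshold in the first case and a different kind of term in the second. The article gives the 0.8 to both aims without this distinction.

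What is at stake is how null results are read. If no taxon passes the FDR cut-off, or no interaction is significant, a reader relying on the power section could take that as a negative from an adequately powered study. The article does not say it will interpret null results that way, but nothing in the power statement prevents it.

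**Working it through.** **Inputs from the article.** 160 evaluable infants, power 0.8, α = 0.05, medium effect (f² = 0.15), 100 simulations per plotted point, hundreds of taxa, FDR 5%.

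**Assumptions.** Two-sided tests; m = 100 to 500 taxa; independent tests; 5–20% of taxa truly associated where several signals are considered; each true taxon has the same per-test effect as the powered main effect; the interaction is 1/4 to 1 times the main effect on the standardised scale.

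**Step 1: can the 160 be reproduced?** Not exactly. The prevalence of RWG, the random-effect variance, the mapping from f² to log-odds and the term tested are not given, and Fig. 2 is not shown. Two cross-checks:
- A linear-regression F test at f² = 0.15 with three predictors needs 57 infants (1 df) or 77 (3 df), and has power above 0.98 at 160. It does not reproduce 160.
- An infant-level logistic simulation at n = 160 (400 runs per setting; log-odds 0.5–0.6 per SD and RWG prevalence 25–50%, both assumed) gives main-effect power of 0.69 to 0.92. So 0.80 is plausible for one main effect, and it is taken as given below.

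**Step 2: noncentrality implied by the stated power.** δ = z(0.975) + z(0.80) = 1.960 + 0.842 = 2.802.

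**Step 3: Aim 2, one associated taxon.** A lone signal must reach p ≤ 0.05/m, so power ≈ Φ(δ − z(1 − 0.05/(2m))). The infants needed to restore 80% are 160 × ((z(1 − 0.05/(2m)) + 0.842)/2.802)².

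| m | critical z | power | infants for 80% |
|---|---|---|---|
| 100 | 3.481 | Φ(−0.679) = 0.25 | 381 |
| 200 | 3.662 | Φ(−0.861) = 0.19 | 414 |
| 300 | 3.765 | Φ(−0.963) = 0.17 | 433 |
| 500 | 3.891 | Φ(−1.089) = 0.14 | 457 |

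**Step 4: Aim 2, several associated taxa.** Benjamini–Hochberg relaxes the cut-off as rejections accumulate. Simulating m independent z-statistics with the true ones shifted by δ gives average power per true taxon of about 0.29–0.33 when 5% are associated, about 0.40 at 10% and about 0.51 at 20%. The chance of detecting at least one true taxon is about 0.78 at its lowest (m = 100, 5 associated) and approaches 1 elsewhere in the range.

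**Step 5: Aim 3, one interaction at 0.05.** With r the ratio of the interaction's standardised effect to the main effect's, power = Φ(rδ − 1.960).
- r = 1: Φ(0.842) = 0.80
- r = 3/4: Φ(2.101 − 1.960) = 0.56
- r = 1/2: Φ(1.401 − 1.960) = 0.29; 80% would need 160/0.25 = 640 infants
- r = 1/4: Φ(0.700 − 1.960) = 0.10

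The logistic simulation of Step 1, with an interaction term added, agrees in direction: 0.52–0.79 for an interaction equal to the main effect in log-odds per SD, and 0.18–0.32 at half. Controlling multiplicity over many GM × sleep pairs would lower these figures.

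**Step 6: simulation precision.** The Monte Carlo standard error at 0.8 with 100 replicates is √(0.8 × 0.2/100) = 0.04, so a plotted 0.80 is compatible with about 0.72–0.88. This is secondary to Steps 3–5.

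**The case against.** Several counter-arguments have force.

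- *The 0.8 does fit part of Aim 2.* The Aim 2 hypothesis begins with lower GM diversity, and the simulated predictor is a GM diversity variable. A reader might infer that the stated power applies to neither aim; the article does not support that. The gap concerns the taxon-level rule and the interaction. Still, the Statistical analyses section names no single overall diversity test as the one that was powered.
- *The powered term is not named and the figure is not shown.* This is correct, so the absence of an interaction is inferred from the listed model terms. Whether the GM or the sleep term was read, each is a main effect, and the mismatch remains.
- *The authors foresee the problem.* The Aim 3 text concedes that many variables can cost power and sets a nested fallback: carry forward significant variables, cluster them, and test interactions only within mixed clusters. Aim 2 also prunes redundant taxa by AIC. These steps reduce the number of tests or findings, but Aim 3 still ends in interaction tests, and neither step enters the calculation of 160.
- *The lone-taxon figure is the worst case.* This is fair. With several associated taxa, finding at least one is likely, as Step 4 shows. With a large effect (f² = 0.35, noncentrality scaled by √(0.35/0.15) to 4.28), lone-taxon power would be 0.65–0.79. The 160, however, is quoted for the medium effect.
- *Outcome structure.* A reader might infer from the mixed-effect model with six repeated measures that six RWG outcomes per infant were simulated. The article attributes the six measures to the predictors and does not say how the outcome was generated, so that inference is unsupported and the point does not rely on it.

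**Conclusion.** The stated power is wrong as attached to Aims 2 and 3 without qualification. It can stand for one overall GM-diversity or sleep main effect at 0.05. Under the taxon-level rule the same effect has power of about 0.14–0.25 for a lone taxon and about 0.3–0.5 on average per true taxon. For the interaction, 0.80 holds only if its standardised effect matches the powered main effect, and power falls to 0.56 at three quarters and 0.29 at half.

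These sizes depend on the assumed number of taxa, the share associated, independence between tests and the interaction ratio, none of which the article gives; real taxa are correlated. The direction is less sensitive: per-taxon power stays well below 0.8 across the whole range examined, and interaction power is below 0.8 at any ratio under 1. The analyses themselves remain usable; the power claim is what needs correcting.

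**What to change.** In the power section, state that the 0.8 covers one named GM-diversity main effect at α = 0.05, and name that index in the Statistical analyses section as the powered Aim 2 test. Then do one of the following for the taxon-level FDR tests and the sleep × GM interactions:

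- label them exploratory; or
- quote power simulated under their actual decision rules (Benjamini–Hochberg over the expected number of taxa, and an explicit interaction term), preferably with more than 100 replicates per point.

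The first option is a change of wording. The second needs an extended generating model, so it is some real simulation work. Either way the stated power becomes less favourable, and in the first option the Aim 3 interaction test loses its confirmatory label. No added enrolment is needed. The article reports recruitment and follow-up as ongoing, so the change can be made before analysis.
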